**Method:**

We will enroll 76 patients with advanced lung cancer into an eHealth ecosystem of stepped and personalized psychosocial care for 9 months. These patients will be compared with another 76 receiving usual care in a non-inferiority randomized controlled trial. The following main outcomes will be measured every 3 months: emotional distress, spirituality, demoralization, quality of life, and medication adherence. Secondary outcomes will include symptomatology, health education, cost-utility analyses, usability and satisfaction with the platform, and time to detect emotional needs and provide care. Baseline differences between groups will be measured with the Student *t-*test or chi-square test, as appropriate. We will then compare the main outcomes between groups over time using multilevel linear models, report effect sizes (Hedges' *g*), and assess non-inferiority. The cost-utility of both interventions will be considered in terms of quality adjusted life years and quality of life given the costs of providing each treatment.

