### Aims and hypotheses

1.1

The main objective of the project is to implement and evaluate the efficacy of a stepped online ecosystem for detecting, following, and addressing the psychosocial needs of patients with lung cancer and to compare those with usual face-to-face treatment. We aim to detect cases at risk of significant emotional distress and decrease the time to access appropriate psychosocial care when using eHealth and usual face-to-face care.

Comparisons between the two interventions will consider the effects on ameliorating the psychosocial consequences of lung cancer and its treatment on emotional distress, demoralization, QoL, and medication adherence, including consideration of the role of spirituality and patient perception of their health education. The cost-utility of each intervention will then be analyzed in terms of quality adjusted life years (QALYs), considering use of additional health services, consumption of psychotropic drugs, sick leave durations, professional salaries, and infrastructure and transportation costs. We will then measure perceived satisfaction and usability of the eHealth ecosystem. Finally, the cases at risk of emotional distress will be detected earlier than treatment as usual. Consequently, using new technologies, we will decrease the time to access appropriate psychosocial care.

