Considering previous results, the literature reviewed, and the objectives set forth, we hypothesized that two psychosocial treatments will improve emotional distress, demoralization, QoL, and medication adherence. Moreover, these improvements will be greater in patients with worse psychosocial results at baseline. For patients with a better baseline status, we expect the psychosocial interventions to exert a buffering effect despite disease progression. The eHealth ecosystem will obtain results equivalent to usual care for emotional distress, demoralization, QoL, and medication adherence. Spirituality at baseline, or its augmentation by psychosocial interventions, will predict better outcomes for emotional distress, demoralization, QoL, and medication adherence. Health education will improve markedly in the group allocated to the eHealth intervention. Compared with usual care, eHealth will have a superior cost-utility in terms of QALYs. Finally, users will be satisfied with the eHealth ecosystem and will perceive it as easy to use. The eHealth ecosystem will significantly improve the time to detection, intervention, and resolution of clinically significant psychosocial need compared to usual care.

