##### Early detection of patients at risk of emotional distress and time to receive appropriate psychosocial care

2.5.2.3

Well-being - emotional discomfort screening: it will be evaluated through an emotional state thermometer with a response system in VAS format, which will be scheduled weekly on the ICOnnecta't platform (see Fig. 2).

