**Fig. 2 f0010:**
[figure not shown]
Stepped digital psychosocial intervention ICOnnecta’t.

The number of detected clinical cases: in the EG this will be obtained through the number of potential clinical cases recorded throughout treatment (VAS ≥6). In CG it will be obtained through the number of clinical cases recorded in the follow-up of face-to-face visits or if the patient reports a worsening by telephone and the visit is brought forward to confirm if it is a clinical case (VAS ≥6).

Waiting time to provide psychosocial intervention: In the EG, the time between the occurrence of a potential clinical case (VAS ≥ 6) and the start of psychosocial intervention will be assessed. The CG will assess the time between the face-to-face screening visit that confirms the clinical case and the next face-to-face visit.

Percentage of resolved psychosocial cases: in both groups it will be obtained through the number of clinical cases that are resolved.

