### Planned statistical analysis

2.9

Descriptive analyses will be performed using Student t or chi-squared tests, as appropriate. This will include assessment of sociodemographic and clinical variables at baseline, together with any pre-treatment differences between groups. Intention-to-treat analyses will then be performed through multilevel linear models to compare both groups on each primary outcome: emotional distress (HADS), demoralization (DS-II), QoL (FACT-L), and medication adherence (ARMS-e).

The modeling process will be parsimonious and guided by fit indexes, starting with a model using the time and type of therapy as fixed predictors. Then, random effects will be tested, and the interaction between time and type of therapy, the eHealth step reached, symptomatology (ESAS-r), and spirituality (FACIT-Sp) will be progressively entered as predictors. The estimation method will be maximum likelihood. Effect sizes (Hedges' g) will be reported for the primary outcomes and non-inferiority will be assessed for the HADS by comparing the means of both groups at T2 and T3. Additional multilevel linear models will be run to assess changes in health education (VAS) between groups, according to the same procedures. As for the cost-utility analyses, the EQ-5D will be used to compute the QALYs together with associated costs for medical care, psychotropics, sick leave, professional salaries, infrastructure, and transportation.

Descriptive analyses will also be conducted for platform's satisfaction and usability (VAS), as well as for participants reaching each step in the eHealth group. Mean differences in the number of clinical cases detected (according to the emotional thermometer), waiting time to provide care, and number of clinical cases solved will then be compared between groups by Student *t*-tests. For the reporting of results, 95 % confidence intervals will be provided. Analyses will be performed using IBM SPSS version 24 (IBM Corp., Armonk, NY, USA) and R software, with support provided by the biostatistics department of IDIBELL.

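### Earlier detection and faster resolution are hypothesised, but the planned outcomes are a count of detected cases and a count of solved cases; only the wait from detection to care is timed

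*Protocol article*

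**What the plan says.** **What is promised.** The Abstract (Method) lists "time to detect emotional needs and provide care" among the secondary outcomes. Section 1.1 (Aims and hypotheses) says that "the cases at risk of emotional distress will be detected earlier than treatment as usual", and closes with the hypothesis "The eHealth ecosystem will significantly improve the time to detection, intervention, and resolution of clinically significant psychosocial need compared to usual care".

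**What is measured.** Section 2.5.2.3 defines three quantities.
- Detected cases. For the eHealth arm (EG), "in the EG this will be obtained through the number of potential clinical cases recorded throughout treatment (VAS ≥6"). For control (CG), "In CG it will be obtained through the number of clinical cases recorded in the follow-up of face-to-face visits", or after a telephone report that brings a visit forward.
- Waiting time. In EG it runs from the positive thermometer to the start of intervention. In CG it runs from the confirming visit to the next visit.
- Resolution. "Percentage of resolved psychosocial cases: in both groups it will be obtained through the number of clinical cases that are resolved".

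**What is analysed.** Section 2.9 compares the number of cases detected by t-test, and adds that "waiting time to provide care, and number of clinical cases solved will then be compared between groups" by the same test.

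**How often each arm is looked at.** The EG thermometer is one "which will be scheduled weekly on the" platform. Section 2.6.2 gives control an average of seven sessions, 2–3 weeks apart.

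**The concern.** A count carries no information on when something happened. If the arms detect equal numbers, one early and the other late, the planned comparison shows no difference. If one arm detects more, that does not show that it detected sooner. The single timed outcome begins at detection, so it cannot measure how long detection took, and no defined interval ends at resolution.

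The second difficulty is that resolution is called a percentage in section 2.5.2.3 and is a number in section 2.9. An arm that is screened more often can find more cases and so solve more, even if each case is no more likely to be resolved.

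Quicker access to care is a stated aim and part of the rationale for the platform. A difference in counts could be read as support for a claim about speed or success that the analysis does not address.

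**Working it through.** The article gives no expected figure for detection or resolution, so there is none to reproduce. The sample size of 152 (76 per arm, section 2.7) is derived for the HADS and is used below only as the number per arm.

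**Step 1: match each hypothesised time to an outcome.**

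| Time in the section 1.1 hypothesis | Outcome in 2.5.2.3 | Analysis in 2.9 | Does it measure the time? |
|---|---|---|---|
| Detection | Number of detected cases | t-test on the number | No |
| Intervention | Wait from detected or confirmed case to care | t-test on the wait | Yes |
| Resolution | Percentage resolved | t-test on the number solved | No |

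**Step 2: a count does not see timing.** Assume that both arms detect 30 cases, one at a median of week 4 and the other at week 12. The difference in counts is 30 − 30 = 0, while detection is 8 weeks apart.

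**Step 3: opportunities for detection differ.** The Abstract gives 9 months in the eHealth programme, which is 9 × 52/12 = 39 weeks and so up to about 39 weekly thermometers. In control, seven sessions have six gaps, spanning 6 × 2 = 12 to 6 × 3 = 18 weeks. Seven is an average, and control patients may also telephone, so this shows the direction of the imbalance and not its exact size.

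**Step 4: number against percentage.** Number solved = number detected × proportion resolved. All inputs are assumed.

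| EG detected, resolved | EG solved | CG detected, resolved | CG solved | Number favours | Percentage favours |
|---|---|---|---|---|---|
| 40, 60% | 24 | 20, 60% | 12 | EG | neither |
| 40, 50% | 20 | 20, 70% | 14 | EG | CG |
| 30, 60% | 18 | 20, 70% | 14 | EG | CG |
| 25, 60% | 15 | 20, 70% | 14 | EG | CG |

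**Step 5: how often the planned t-test would be significant.** The simulation used 76 per arm, at most one case per patient, no dropout and 4,000 runs.
- 40 against 20 detected, 60% resolved in both arms: EG favoured at p < 0.05 in 63.6% of runs.
- 40 against 20 detected, 50% against 70% resolved: EG favoured in 21.2% of runs.
- 50 against 20 detected, 50% against 70% resolved: EG favoured in 53.1% of runs.
- 20 detected and 60% resolved in both arms: significant in 2.4% of runs for EG and 2.7% for CG, as expected by chance.

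The first result can be checked by hand. The proportions solved per patient are 24/76 = 0.316 and 12/76 = 0.158, a difference of 0.158. The standard error is √(0.316 × 0.684/76 + 0.158 × 0.842/76) = 0.068. The ratio is 2.33, and the chance of exceeding 1.96 is about Φ(2.33 − 1.96) = Φ(0.37) = 0.64.

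**The case against.** The strongest reply has four parts.

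- **A time is measured.** This stands. Waiting time to intervention is defined in both arms and analysed. A reader might infer that the section holds no time measurement at all; the article does not support that.
- **Detection dates must exist.** This also stands. The waiting-time clock starts at detection and T0 is fixed, so time to detection is a subtraction. A reader might infer that the trial could never test the detection hypothesis; that is too strong. A condensed article may leave the definition of a derived variable to a fuller document. Here, however, it names the outcome and the test, and both are counts. Carrying out those sections faithfully would still yield no time to detection.
- **Resolution rests on one sentence.** Largely true. The detection aim in section 1.1 and the secondary outcomes in the Abstract do not mention resolution. The hypothesis could be read as three separate items, with only detection timed. The more natural reading applies time to all three, and under either reading section 2.9 analyses a number where 2.5.2.3 names a percentage.
- **The number may simply be the numerator.** Possible. The number detected is also reported, so an attentive reader could form the ratio. The test is nevertheless planned on the number. A reader might infer that the resolution result will reverse; the article gives no counts or rates, so reversal is only a possibility.

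**Conclusion.** The mismatch is real and lies inside the article. It promises earlier detection in three places and, on the natural reading of one sentence, faster resolution. Time to intervention is covered; time to detection and time to resolution are not.

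The number solved is inconsistent with the percentage defined earlier and mixes how many cases were found with how well they were resolved. The size of that effect depends on assumed inputs: with twice as many cases detected and equal resolution, about 64% of simulated trials would favour eHealth. The direction rests on weekly screening finding more cases than visits 2–3 weeks apart, which is plausible but not established.

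These are secondary outcomes. Neither the HADS non-inferiority test nor the sample size is affected. The wording and the analysis should be reconciled before results are known.

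**What to change.** In sections 2.5.2.3 and 2.9:

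1. Add time from T0 to the first recorded case (VAS ≥ 6) for every randomised patient, using the detection dates that the waiting-time outcome already needs. Treat death as a competing event, since the population has stage III–IV lung cancer. State that the comparison includes the effect of different screening frequency.
2. Replace the number of cases solved by the percentage resolved among detected cases, shown with its denominator. Label it descriptive, because detection happens after randomisation and the intervention itself can change who is detected.
3. Support it with the proportion of all randomised patients with HADS ≥ 10 at T1, T2 and T3. The scheduled HADS is collected in the same way in both arms, and 10 is the article's own cut-off. This is not a time to resolution: it uses a different case definition from the thermometer and is observed only every 3 months.

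In section 1.1, remove resolution from the time hypothesis or restate it as the percentage resolved, and bring the Abstract into line with the outcomes kept.

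Cost: a little more analysis work and a narrower claim about resolution. The dates and the HADS forms are already part of the plan, so no new data collection is needed.

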## Material and methods

2

### Study design

2.1

This study proposes a randomized non-inferiority trial of an eHealth ecosystem compared to usual psychosocial care. The main outcomes will be assessed at baseline (T0), 3 months from T0 (T1), 6 months from T0 (T2), and 9 months from T0 (T3). Therefore, the design comprises two treatment conditions and four assessments. We chose the non-inferiority based on a literature review that indicated mixed and inconsistent results when comparing eHealth and face-to-face psychosocial interventions in cancer (Merluzzi et al., 2019; Singleton et al., 2022; Wang et al., 2020; Xu et al., 2019). Therefore, we do not hypothesize that our eHealth ecosystem will be more efficacious than usual care, but instead, aim to show that it is at least not inferior in terms of efficacy and efficiency. The methodology will adhere to the principles of Responsible Research and Innovation (RRI, European Commission, Directorate-General for Communication, 2013).

### Participant recruitment and procedure

2.2

Participants will be recruited through different healthcare units (e.g., the Functional Lung Unit and the General Palliative Care Outpatient Service at ICO). When clinicians from these services identify a patient who meets the inclusion criteria, they will contact researchers from ICO's eHealth program, who in turn, will contact the patient (See Fig. 1 for details of recruitment).

**Fig. 1 f0005:**
[figure not shown]
Flowchart of the recruitment process and study follow-up assessments. See questionnaires details below (2.5 Measures).

### Inclusion and exclusion criteria

2.3

Individuals agreeing to participate will be screened to verify whether they meet all the following inclusion criteria: age ≥ 18 years; recent diagnosis (<3 months) of advanced lung cancer (stage III–IV); internet access and digital experience; and ability to read, write, and speak Spanish. The exclusion criteria will include current major depressive episodes, risk of self-harm, active psychotic symptoms, and substance abuse.

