## Introduction

1

Lung cancer affects >2 million people worldwide each year and has a 5-year patient survival of only 13 % (Sung et al., 2021). Estimates in the European Union indicated that there had been 318,327 new cases in 2020, marking the lung as having the highest mortality of 20.4 % of all cancer-related deaths (European Union, 2021). Affected patients also frequently encounter severe symptoms that show a variable and erratic course over time and make the illness course highly unpredictable. Consequently, these patients tend to have a very poor quality of life (QoL), especially in advanced stages (Presley et al., 2020), and up to 63 % experience clinically significant psychological distress (Graves et al., 2007; Lv et al., 2021). Indeed, a recent survey of over 9000 patients with lung cancer indicated that most functional limitations were due to pain (68.6 %) or emotional distress (48.3 %) that remained untreated in 32.5 % (Presley et al., 2020). Psychosocial care is generally inadequate, with many patients having no possibility of receiving appropriate care. Given that this distress does not remit over time (Aubin et al., 2022), it is urgent that we improve screening, offer close and intensive follow-up, and refer to adequate and accessible services early.

Palliative care refers to the medical relief typically offered to people living with incurable illnesses, and for those with advanced lung cancer, it typically focuses on common physical symptoms like fatigue, dyspnea, and chronic pain (Rajapakse, 2021). Over recent decades, however, the value of addressing a person's psychosocial and spiritual needs has also been recognized. American and European societies for medical oncology now advocate the integration of early psychosocial palliative care in standard oncology practice for patients with metastatic or advanced disease. This decision has been supported by the results of a recent meta-analysis (Fulton et al., 2019), which demonstrated that palliative interventions with physical and psychological aspects can benefit a patient's short-term QoL and overall symptom burden. Evidence suggests that a patient's emotional distress is associated with not only poorer QoL but also lower adherence to treatment and the adoption of unhealthy lifestyles (Jansen et al., 2017). Despite this growing evidence, emotional distress is not always considered in palliative care, leaving many patients with undetected and unresolved psychosocial needs.

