### Power analysis

2.7

The sample size has been estimated using R software, setting a non-inferiority margin of 5 points on the HADS (Vaganian et al., 2020) with a power of 80 % and a one-tailed α of 2.5 %. Assuming a dropout rate of 25 %, we require 152 participants (76 per branch) to ensure a 95 % bilateral confidence interval that excludes the non-inferiority threshold.

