## Discussion

3

The current protocol describes a randomized controlled trial intended to examine whether a stepped-care, eHealth-based psychosocial intervention can effectively detect and address the psychosocial needs of patients with advanced lung cancer. We plan to conduct an open-label randomized controlled trial in two groups: one receiving an individualized online stepped-care psychosocial intervention, and the other group receiving an average of seven face-to-face visits with a clinical psychologist.

Patients with lung cancer are mostly diagnosed at advanced disease stages and have minimal prospect of cure. Such a scenario produces stress and psychological trauma for many patients, which in turn, affects their QoL (Liegey Dougall et al., 2017). Given that effective palliative care should improve the QoL of patients and their families, tackling their psychosocial needs in an efficient manner should be among the top priorities of comprehensive palliative care. Health education (Yu et al., 2022) and psychosocial care (Jansen et al., 2019) can both mitigate the emotional distress of a diagnosis and improve QoL among patients with lung cancer. However, the limited access to such care presents an important barrier (Travado et al., 2017).

The use of eHealth can overcome barriers requiring physical attendance at health centers with symptoms of fatigue, dyspnea, or pain (Rajapakse, 2021). As ICTs have emerged to deliver psychosocial interventions reliably to vulnerable patients with advanced cancer (Penedo et al., 2020), clinicians and researchers have begun to study techniques to deliver palliative interventions in an eHealth format (Chua et al., 2019; Gómez-Batiste et al., 2014). However, existing research has usually centered on physical symptoms, not the emotional and spiritual concerns of patients. Furthermore, patients benefit most from psychosocial interventions when they have elevated baseline emotional distress (Jansen et al., 2019; Medina et al., 2022; Nissen et al., 2021), stressing the importance of individualized strategies that allocate resources to patients with at-risk profiles.

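### The only stated non-inferiority test pools patients with and without distress, so its result cannot support a claim about distressed patients

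*Protocol article*

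**What the plan says.** - **Entry (section 2.3).** Beyond age and Spanish, the requirement is "recent diagnosis (<3 months) of advanced lung cancer (stage III–IV); internet access and digital experience". No HADS, thermometer or ENP-E level is needed. The upper end of distress is trimmed: "The exclusion criteria will include current major depressive episodes, risk of self-harm, active psychotic symptoms, and substance abuse".
- **Margin (section 2.7).** There is one margin for the whole sample: "setting a non-inferiority margin of 5 points on the HADS".
- **Test (section 2.9).** HADS non-inferiority is judged from the two arms' means at T2 and T3. The predictors listed for the multilevel models are time, therapy, their interaction, eHealth step reached, ESAS-r and FACIT-Sp. T0 HADS is not among them, and no estimate in distressed patients is described.
- **Expected pattern of benefit.** The Discussion says that "patients benefit most from psychosocial interventions when they have elevated baseline emotional distress". Section 1.1 expects larger gains in patients with worse baseline results, and mainly protection against decline in the others.
- **How common distress is.** The Introduction reports that "up to 63 % experience clinically significant psychological distress".
- **Cut-off (section 2.5.1).** A total HADS of 10 or more marks moderate distress. The same score is part of the rule for leaving eHealth Level 1 (section 2.6.1.1).

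**The concern.** In a non-inferiority trial, patients in whom the two treatments can hardly differ pull the arms together and make success easier to declare. By the protocol's upper figure, at least 37% of entrants have no clinically significant distress. Those with a low T0 HADS have little room to improve in either arm, although they may worsen and be escalated later.

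The main objective in section 1.1 is to detect and address psychosocial need, and the comparator in section 2.6.2 is individual psychotherapy averaging seven sessions. A positive result could easily be taken to mean that stepped eHealth can replace that therapy in patients who need it. The stated test averages over everyone, so it does not answer that question. The section 1.1 hypothesis about baseline severity also has no matching term in the section 2.9 model.

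**Working it through.** **Inputs**
- From section 2.7: margin 5, power 80%, one-sided alpha 2.5%, and "Assuming a dropout rate of 25 %, we require 152 participants (76 per branch"). Evaluable per arm: 76 × 0.75 = 57.
- Share distressed p = 0.63, from the Introduction, where it is an upper figure. It is assumed here to match T0 HADS of 10 or more.
- SD of HADS: not stated in the article. It is back-solved below; SD 7 is used as an assumed alternative.
- Illustrative truth: eHealth is 5 points worse in distressed patients and equal in the rest.

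**The plan's own sample size**

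n per arm = 2 × SD² × (1.960 + 0.842)² / (5 − true difference)².

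With n = 57 and a true difference of 0, SD = 5 × √(57/2) / 2.802 = 9.53. Then 57 / 0.75 = 76 per arm, 152 in total. This is a back-solution, not an independent reproduction. SD 7 fits equally well if a true difference of 1.33 was assumed: 5 − 7 × 2.802 × √(2/57) = 1.33.

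**Dilution**

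Pooled deficit = 5 × 0.63 + 0 × 0.37 = 3.15 points.

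**Chance of declaring non-inferiority at one time point**

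P = Φ((5 − pooled deficit) / SE − 1.96), with SE = SD × √(2/57).
- SD 9.53: SE = 1.785; 1.85 / 1.785 − 1.96 = −0.924; P = 17.8%.
- SD 7: SE = 1.311; 1.85 / 1.311 − 1.96 = −0.549; P = 29%.
- All patients distressed: pooled deficit 5; P = Φ(−1.96) = 2.5%.

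**Sensitivity at SD 9.53**

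| Change to the illustration | Pooled deficit | P |
|---|---|---|
| None | 3.15 | 17.8% |
| Low-distress eHealth patients also 2 points worse (3.15 + 2 × 0.37) | 3.89 | 9% |
| T2 and T3 must both pass (correlation 0.5 to 0.7 assumed) | 3.15 | 7–10% |
| Either T2 or T3 suffices (same correlations) | 3.15 | 26–28% |
| Share distressed 50% (assumed) | 2.50 | 29% |

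A simulation on the bounded 0–42 scale, with low-distress patients near the floor, gave 31% at 63% distressed (resulting SD about 6.7) and 2.5% with all patients distressed. This agrees with the formula.

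**Precision of an estimate in distressed patients**

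Evaluable per arm = 57 × 0.63 = 35.9, about 36. The 95% half-width is 1.96 × SD × √(2/36), which is 3.2 points at SD 7 and 4.4 at SD 9.53. Power to exclude 5 points at a true difference of 0 and SD 9.53 is Φ(5 / (9.53 × √(2/35.9)) − 1.96) = Φ(0.263), about 60%.

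**The case against.** The trial asks about patients with advanced lung cancer, not about distressed patients. For that population a true deficit of 3.15 points lies inside the margin, so declaring non-inferiority is correct. **This stands.** A reader might set 18–29% against 2.5% and infer an inflated false-positive rate. The documents do not support that: the two figures belong to different estimands, and the larger ones are power within the non-inferior region of the all-comer question.

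Other stronger readings also fail:
- A reader might infer that low-distress patients cannot contribute or never leave Level 1. Section 2.6.1.1 schedules a weekly thermometer that can start escalation at any time. Section 1.1 expects protection against decline, so the arms can also differ through new distress. Section 2.6.2 states no distress threshold for the control sessions. A zero difference in these patients is therefore only an assumption.
- The Introduction's 48.3% might be taken as a second prevalence. It describes functional limitations attributed to emotional distress and is not used here.
- The sample should not be called mostly free of distress. At up to 63%, distressed patients may be the majority.
- Whether the 5-point margin was derived for distressed patients cannot be judged from the article, which only cites a source for it.

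Two further objections carry weight. All-comer entry suits a programme built on screening and monitoring. Supportive subgroup estimates are also often left to the analysis plan, which is not shown. This limits the point to what the stated test can support. It does not remove it, because section 2.9 names the test and lists the predictors, and section 1.1 raises a baseline-severity hypothesis that those predictors do not cover.

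**Conclusion.** The point holds as a limit on what the trial can conclude. It is not an error in eligibility or in the error rate of the planned test. Under the illustration, an eHealth arm worse by the whole margin in distressed patients would still be declared non-inferior overall in roughly one trial in six (SD 9.53) to three in ten (SD 7). The chance falls to 7–10% or 9% under the stricter scenarios, and rises if fewer than 63% are distressed. Excluding major depressive episodes could lower that share.

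The figures rest on an unstated SD, an upper-bound prevalence, and no difference between arms in low-distress patients. The qualitative conclusion needs less: in every scenario checked that includes undistressed patients, the chance exceeds the 2.5% that would apply if distressed patients were tested alone. A pooled success therefore cannot be carried over to them.

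**What to change.** Keep enrolment as it is and change section 2.9:
1. Add T0 HADS and an arm-by-T0-HADS term to the HADS model, allowed to vary by visit so that estimates at T2 and T3 follow. This also supplies the baseline-severity term that the section 1.1 hypothesis needs.
2. Pre-specify the arm difference with 95% CI in patients with T0 HADS of 10 or more, the protocol's own cut-off. Show it against the 5-point margin as a supportive estimate.
3. State that the primary non-inferiority conclusion applies to the unselected enrolled population, which includes many patients without distress, and that it is not extended to distressed patients unless that interval supports it.

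**Cost.** Only the analysis text and the wording of the conclusion change, since T0 HADS is already collected. The drawback is imprecision: at most about 36 evaluable per arm in that group, fewer if distress is less common. The interval may therefore fail to exclude 5 points even if the arms are truly equal, which is why the estimate is better kept supportive than made a second formal hurdle.
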